## Abstract

**Background:**

Due to its association with multimorbidity, frailty gives rise to multidimensional needs for different services. Too often, patient preferences and service encounter information are not adequately shared.

**Objective:**

This developmental study aims to co-design, collect, and analyze encounter data from multiple community and primary-based multidisciplinary teams (MDTs) providing services for people with frailty to develop prototype large language models that can generate clinical and person-centered care summaries.

**Methods:**

Engaging stakeholders in 2 primary care networks, we will co-design the large language model to ensure it meets local needs and preferences as well as infrastructure, information governance, and regulation requirements. General practitioners will identify 50 patients with frailty requiring MDT engagement. Three consecutive encounters between the patients and different members of MDTs will then be audio-recorded. Recordings will be transcribed into text for concept design and model pretraining. These data combine stakeholder engagement insights to develop sensitive artificial intelligence (AI) models responding to stakeholders’ needs, workflows, and preferences. To generate the person-centered summaries, we will test 2 approaches to modeling the encounter data: graph-based modeling and hierarchical transformers. The AI-generated summaries will be compared to human-written summaries of the same encounter data and assessed for accuracy, quality, fluency, and person-centeredness. They will also be shared with the original MDT members for validation. We will capture inputs, processes, and outcomes across all key phases of the implementation journey to identify capability requirements, determinants of implementation (including key challenges and best practices to overcome them), and the value added by the technology.

**Results:**

This protocol aims to review implementation evidence and engage stakeholders in co-design. This work package will aid the development of contextually sensitive, longitudinal, and AI-generated person-centered summarization tools. Model development will aim to achieve longitudinal person-centered summaries tested against MDT standards. If deemed suitable for deployment, optimum ways of integrating these summaries into shared care records will be explored with local key system leaders. Model evaluations will provide conclusive insights into such technologies’ benefits and risks. As of August 2025, this study has not yet been funded, nor has ethical approval for the project been obtained. Consequently, dates of data collection and numbers of recruited participants are not applicable at this time.

**Conclusions:**

Our protocol provides a robust method of co-designing, evaluating, and implementing a longitudinal AI medical summary tool. Including key stakeholders at multiple stages facilitates an iterative development strategy that is designed to solve implementation challenges as they emerge. This project fits within our long-term vision to deliver a multimodal AI tool that saves clinicians time and deepens the health care professional–patient relationship. Future studies should include a larger patient sample, video-recorded health care professional–patient encounters, and a more extensive longitudinal evaluation.

**International Registered Report Identifier (IRRID):**

PRR1-10.2196/68511

## Introduction

### Background

Due to its association with multimorbidity, frailty gives rise to multidimensional needs for different services [1-4]. To reduce fragmentation and duplication of services and enhance person-centered care (PCC), information about patients’ clinical needs, service encounters, and preferences should be shared across multidisciplinary teams (MDTs). Too often, this information is neither adequately recorded nor shared [5,6].

Evaluation of a “what matters to you” (WMTY) initiative for patients with frailty in one of our local trusts found that WMTY conversations were often happening too late and in the wrong setting (hospital as opposed to primary or community setting), did not always involve the right people (eg, general practitioners [GPs] and voluntary sector and care workers), were subject to key trade-offs concerning staff time (eg, peripatetic community staff working in geographically dispersed settings entering encounters notes at the end of the day), and were not shared with other members of the MDT. Indeed, due to organizational pressures prioritizing patient flow, many WMTY conversations are overly focused on facilitating hospital discharge.

However, important conversations are happening every day with members of MDTs (GPs, community nurses, social workers, domiciliary carers, volunteers, and pharmacists) from the community to hospital settings. Too often, this information is neither adequately recorded nor shared, leaving an untapped source of valuable information about patients’ needs, beliefs, and personalized goals. Artificial intelligence (AI) tools such as large language models (LLMs) have been used to have a good effect on the summarization of synthetic patient-physician conversations [7]. However, these models tend to focus on clinical needs, drawing from notes written after a conversation, and offer little more than physicians' usual clinical summaries. Summarization models are needed to generate automatic summaries that include clinical needs and WMTY information from multiple MDT consultations without recall bias from health care professionals (HCPs).

Previous research and funding efforts have laid the groundwork for this proposal. We received support from the National Institute for Health and Care Research Invention for Innovation Funding At the Speed of Translation program to validate LLMs for generating automatic person-centered (PC) summaries of GP consultations [8]. Extensive engagement with patients and staff in 3 Plymouth practices and 1 Somerset GP practice informed our understanding that true PCC for this complex group of patients requires a better exchange of clinical and WMTY information into clinical records.

Our project proposes a feasibility study to co-design, collect, and analyze data to develop summarization models using an LLM to generate PC summaries of multiple primary and community service encounters among patients with frailty. Despite the good performance of current large language summarization models [7], implementation is challenging due to a lack of user engagement; ethical, legal, and data governance issues; and poor integration with existing data and workflows [9-11]. Importantly, intelligent data-driven care must also rely on unbalanced, missing, and incomplete clinical data drawn from imperfect real-world settings. Thus, careful preprocessing (eg, cleaning and substituting values) is essential to ensure good predictive modeling and prevent biases and unreliable outputs [12]. Our models, built on patients’ and key stakeholders’ preferences, values, and concerns, will be uniquely designed to generate interoperable PC summaries.

To this end, we will (1) engage stakeholders to understand technical, human factor, ethical, and regulatory barriers and enablers; (2) work with 2 primary care networks (PCNs) to audio record and transcribe primary and community encounters with 50 patients with frailty resulting in at least 150 audio-recorded conversations (eg, 3 encounters per patient); (3) develop and evaluate our LLMs ability to generate gold standard PC summaries that work for patients, carers, and MDT staff; (4) co-design implementation strategies and deploy pilot PC summary data into 2 PCNs; and (5) evaluate the summaries capacity to save HCPs’ time, improve PCC, and patient well-being.

### What Problem Are We Trying to Address?

The geography of older age in the United Kingdom is highly skewed toward coastal and rural areas, such as the Southwest Peninsula [13]. As people age, they experience more ill health and disability, resulting in higher rates of frailty and multimorbidity in these regions compared to urban areas. The British Geriatric Society, Age UK, and the Royal College of General Practitioners advocate for a proactive, PC, coordinated, and community-based response to frailty care [3]. However, individuals with frailty often navigate multiple care pathways, take numerous medications, and interact with various HCPs who do not communicate well with each other [5,6,14-17].

Key advocacy groups emphasize that improving communication between HCPs and emphasizing PCC is crucial to reducing service fragmentation. It is argued that PCC addresses patients’ emotional needs; aligns care with their spiritual and personal beliefs, social activity desires, and self-care goals [18-22]; and creates personalized goals that help reconcile conflicting health objectives across an MDT [23]. At a minimum, then, HCPs should ask, “What matters to you?” instead of “What is the matter with you?” However, in practice, there are concerns that WMTY conversations in acute hospital settings have become overly standardized due to organizational pressures prioritizing patient flow, reducing patient engagement time, and increasing compassion fatigue [14,24,25].

Moreover, these conversations often occur outside the hospital, between patients and their GPs, community nurses, social workers, domiciliary carers, pharmacists, volunteers, and informal carers. They are not adequately recorded or shared. This reduces care continuity across MDTs and overlooks valuable patient information that could enhance shared decision-making [26,27]. Realistically, the health system’s capacity for PCC is reduced because, in acute settings, the pressured context reduces implementation effectiveness, and in community or primary settings, HCPs lack the time to write summary notes covering WMTY and clinical needs.

Finally, many technical requirements remain, and there are potential challenges in building and implementing LLMs in health systems. Particularly, the ethical, practice, cultural, and information governance barriers to recording encounters require close engagement with patients, practitioners, and managers to ensure the feasibility and acceptability of data collection and that summarizations work for all end users [28-30]. Consequently, this project aims to understand and address these AI-related health care implementation gaps.

### Proposed Technological Solution

There is growing interest in generating medical summaries using LLMs to condense complex patient information from text or voice-recorded datasets [7]. For example, LLMs have also shown great potential in summarizing clinical reports [31]. However, only some have reached the quality required for clinical decision-making. In the United States, most summarization tools inform insurance and legal workflows and provide summary information for electronic patient records [32]. We similarly propose developing LLMs to summarize information rather than triggering clinical decisions. Even though multiple LLMs can generate high-quality clinical summaries [7], it is important to note that these models, such as the one used in this study [8], mimic what physicians do (ie, focus on clinical needs) as opposed to PC summaries. Our proposed solution addresses this gap in focus (Figure 1).

**Figure 1 figure1:**
[figure not shown]
A diagram highlighting how the person-centered care (PCC) summarization tool would function. GP: general practitioner; PC: person-centered.

We evaluate whether LLMs can generate PC summaries from audio-recorded patient-physician conversations, fine-tuning the models to develop these summaries and then validating such models [8]. This modeling solves the problem of inadequate capture of PC information. However, achieving PCC requires developing or adapting LLMs for longitudinal summarization from multiple community or primary patient-physician MDT encounters. As part of an integrated, preventive, and community-focused care model, this ensures the meaningful transfer and acceptability of information across MDTs and hospital settings, and mitigates ethical, legal, and governance challenges

If successful, this technology will enhance PC community frailty care. Our PC and clinical data summaries will reduce administrative load, allowing more patient-clinician time in community or primary settings, which is crucial for PCC [5,33]. The synthesis and needs-based distribution of PC encounter data will also improve interoperability, enabling MDT practitioners to access relevant clinical and PC information instantly, reducing service fragmentation, and improving health outcomes [5].

Proactive, anticipatory care for older people with escalating levels of frailty identified in primary care, supported by sufficient capacity for holistic MDT assessment, personalized care planning, and tailored interventions, can also significantly reduce hospital admissions and facilitate earlier discharge [26,27,34-38]. In the National Health Service (NHS) Devon alone, the number of bed days occupied by patients over 75 years old for more than 21 days accounted for 238,340 bed days in 2022, equivalent to 244 beds. Our summarization models could play a significant role in supporting community-focused preventive care.

## Methods

### Overview

We will develop model designs that respond to end users’ requirements regarding usability, interpretability, explainability, risk aversion, and privacy concerns. By integrating end-user feedback and understanding the sociotechnical context, we aim to ensure that our model supports clinical efficiency and wins the hearts and minds of patients and staff. This comprehensive approach will address the unique needs of local populations and foster the adoption of advanced health technologies in diverse health care settings (see Figure 2).

**Figure 2 figure2:**
[figure not shown]
A flowchart summarizing the 5 research stages and their objectives. LLM: large language model.

### Stage 1: Rapid Evidence Reviews

Embedding AI-generated PC summaries into care records is more than a technical exercise. There are feasibility concerns around the initial collection of data (eg, audio recording, staff and patient concerns around privacy, and possible impacts on the nature of encounters), its storage and related information governance requirements (eg, who owns the recording equipment and data), and how summary data should best be presented and integrated into the clinical records. We will undertake a rapid evidence review of AI models focused on patient-clinician research to summarize the current qualitative evidence of common ethical, practice, cultural, and information governance issues. These issues will center upon collecting encounter data (ie, patient-clinician conversation) and integrating summarization AI models into health care systems.

The review aims to understand the best practices and potential barriers to integrating automatic clinician-patient summaries from this rapid review of evidence. This understanding should help establish our models’ data collection, storage, and governance guidelines. It should also provide insights into potential low-fidelity model prototypes, preferences regarding the user-interface functionality, and the types of summaries that fit within existing end users’ workflows and implementation strategies. Finally, this review of evidence will provide a strong coding framework for analyzing the stakeholder engagement section in stage 2.

### Stage 2: Stakeholder Engagement

Two different focus groups will be held with a wide range of stakeholders to co-design and explore the ethical, practical, cultural, and information governance themes around the collection of patient-clinician conversations. Collected data from stage 2 helps form a key part of our participatory, co-design approach to model development and helps with later strategy development for integrating the functional prototype into a health care system. Findings from stage 1 inform the themes explored in the focus groups described subsequently.

Our first focus group’s key stakeholders (n=15) will include patients and carers, voluntary, community, and social enterprise **(**VCSE) representatives, GPs, community nurses, social workers, domiciliary carers, pharmacists, and acute health of older people teams. The discussions are likely to include the following topics: (1) how to embed the AI summarization model into health systems; (2) ethical issues around compliance with UK data privacy laws, AI accuracy and safety standards, measures to safeguard patient-clinician relationships, and clinical autonomy, and minimize biases and medicolegal liabilities; (3) cultural issues, including stakeholders past interactions with AI technologies and ensuring the technology is culturally sensitive and adapts to diverse needs; (4) practical discussions that aim to forecast and address barriers related to relevance, acceptability, and usability of AI summarization models; and (5) how they can be integrated into existing workflows, considering ease of use and integration into daily practices.

Insights from these discussions will guide the refinement of the AI summarization model and inform the development of implementation strategies. We aim to develop a strong understanding of ethical, practical, cultural, and information to code usable, functional LLM models that fit the participating health systems’ existing workflows, cultures, and concerns. From this discussion, we may realize it is important to code specific added measures to safeguard against harm to patient-clinician relationships, clinical autonomy, recall biases, and other medicolegal liabilities.

The second focus group (n=15) will consist of local information governance specialists, IT services, data specialists, managers (hospital, primary care network, and care homes), local authorities, integrated care boards, and regional NHS regulatory boards. This group aims to produce agreements, understandings, and adaptations to improve our models’ viability and likelihood of implementation. The questions will likely explore ensuring wide-scale engagement, senior leadership responsibilities, adapting the basic concept model (Figure 2) to meet localized infrastructural needs, who owns the data collected, where it should be stored, and the potential of these data to be shared and accumulated across multiple nodal points in the MDT. These group discussions then shape model development to meet local data governance standards and agreements on who across the MDT will own the data produced by our LLM, where the data will be stored, and how best to ensure its interoperability. It should also identify senior leadership oversight and responsibilities, and required inputs from MDT managers through development and later implementation.

We know that technologies can fail because of poor design, which stems from a lack of understanding of the actual requirements of the end users. Thus, this phase involves embedding co-design into the project and winning hearts and minds. The stakeholder engagement stage aims to enhance our co-design efforts, creating a truly PC model that addresses the needs of patients, staff, managers, and infrastructure specialists. By improving our co-design process, we can foster support and understanding, ultimately aiding in the successful development and implementation of our model.

### Stage 3: Encounter Data Collection

Audio recordings of encounters between different members of an MDT team and patients with frailty will occur in 2 different PCNs, one between months 6 and 12 and another between months 9 and 15. The first PCN is more experienced in cross-team data sharing and deploying AI solutions and is more prepared to test the feasibility of audio recording encounters than the second PCN, which is more digitally immature. If necessary, access to these patient participants may also be supported by the Clinical Research Network Southwest Peninsula, which can assist the team in contacting other GPs who can help identify suitable and eligible research participants.

Working with GPs, we will identify 50 patients with frailty who require MDT engagement and ensure that MDT members know the project, its aims, methods, and data management protocols. To mitigate the limitations posed by our relatively small sample size, we will apply purposive stratification, ensuring a balanced representative sample across key frailty-associated factors, such as differing clinical frailty scores, typical comorbidity clusters, and social determinants.

To capture a patient’s data from multiple encounters between them and their community-based HCP, the research team will liaise closely with each patient participant and their community carers, encouraging them to provide updates on each future engagement over 2 months to record 3 to 5 consecutive encounters. Each patient will need to agree to participate in at least 3 encounters.

When the researcher is informed of an upcoming encounter, a consenting HCP or patient will notify the researcher of the time, date, and location. The researcher will then attend and record the conversation using high-quality audio-recording devices (Shure SM7B microphones). Patients will need an individual identifier to link encounter data from different MDT members and validate summarizations. Along with these identifiers, each encounter will be identified sequentially, from the first recording to the last. Each patient will participate in at least 3 encounters with HCPs (MDT members), resulting in approximately 150 conversations or encounters. All recordings (with anonymized identifiers) will be transcribed into text for concept design and model pretraining.

### Stage 4: Concept Design, Model Design, and Validation

Data from stages 1 to 3 will be collated, synthesized, and shared with the model developers to adapt an AI summarization model that responds to different stakeholders’ needs, workflows, and preferences.

PC AI summarization has been previously defined by Ponce Ponte [8] as a model capable of summarizing clinical issues as well as patients’ preferences and values. The exact themes of patients’ preferences and values will be derived from further public and patient involvement and engagement (PPIE) with patients and staff in 3 GP practices involved in prestudy PPIE, across 2 counties in southwest England.

Annotators will be trained to generate PC summaries based on audio-recorded conversations between patients and HCPs. This will be carried out following the sequence of a patient’s encounters with their HCP’s (start visit 1, continue to visit 2, etc).

Two approaches have successfully generated automatic summaries from multiple documents: (1) graph-based modeling and (2) hierarchical transformers. On the basis of these approaches, we will adapt our patient-centered AI summarization model [8]. Multiple document summarization approaches are necessary because conversations between patients with frailty and MDT members will accumulate over time. The first model will be developed using graph neural networks, which follow an extractive summarization approach. We will develop a graph structure by encoding words and sentences and generating words and sentence nodes related to an edge. The edge represents how strong their relationship is and will be calculated with the term frequency and inverse document frequency method [39]. This learning will be done per encounter via an iterative process. Once a second encounter is completed, the process will be conducted again. This time, a third level of node will be created, the document node, and this will be included in the learning process to generate a new graph structure. This will continue until the last encounter. After every encounter, we will use the graph structure to extract sentence nodes, follow a trigram blocking for decoding, and generate an extractive PC summary. The training will be done to predict the sequence of sentences from the gold-standard PC summary.

The second model to be tested is based on a hierarchical model. We will develop this by comparing and integrating multiple pretrained LLMs, for example, LLaMA (version 3.1), Falcon, Mistral, and bidirectional encoder representations from transformers and its variants (BioBERT, etc) [40]. Our method to compare these models will require evaluating each using a Recall-Oriented Understudy for Gisting Evaluation ROUGE *F*_1_-score, assessing their capacity to compare PC themes. We will then add a hierarchical adapter on the encoder layer to contextualize sentence semantics or meaning. The overall objective of the model is to predict the next word. Then, to generate the PC summary, we will use retrieval-based selection to choose the most salient content using sentence similarity.

We will automatically evaluate the quality of these summaries using ROUGE *F*_1_-score. This metric compares the AI-generated summaries against our gold-standard summaries. Trained, blinded evaluators will perform human-based evaluations. They will assess their informativeness, fluency, quality, and person-centeredness (number of PC themes captured by the summaries).

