### Stage 5: From Technological Development to Pilot Implementation

After stage 4, we continue to engage with key stakeholders until we reach a saturation level whereby the model’s development either deeply reflects the complexity of localized needs and preferences in the concept design, making the technology more suitable for deployment and integration, or is deemed unfeasible.

Doing this will require repeated prototype engagement and daily discussion sessions with HCPs using the system. This session will be conducted specifically with our first focus group, including patients and carers, VCSE representatives, GPs, community nurses, social workers, domiciliary carers, pharmacists, and acute health of older people teams. Each session will include an introduction explaining the purpose of improving the tool and meeting clinical needs, a brief demonstration, an opportunity to test and use the prototype in small groups, and then report on their experiences. The group of 15 participants will then be subdivided into 5 groups of 3 (20%) participants each and asked to complete the following tasks: use the device to generate a summary based on a prerecorded pseudoanonymized patient-clinician interaction, review its associated AI-generated summary, edit it, and integrate it into an electronic patient record. After completing these tasks, prototype engagement participants will return to the larger focus group to share their experiences, challenges, and suggestions. Topics will likely include ease of use and intuitiveness, clarity and relevance of the summaries, to what extent they could imagine the technology fitting within existing workflows, responsiveness of the tool to correction and feedback, consistency and acceptability of the terminology, and recommendations for enhancements. This process will be repeated at least twice but primarily until saturation is reached, which is defined as broad HCP satisfaction with the usability of the devices.

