### Stages 3 and 4: Model Development and Validation

This stage collects audio recordings from approximately 150 MDT encounters with 50 purposively sampled patients with frailty. By collecting 3 consecutive encounters with each patient, we will yield a robust dataset for beginning to test, train, and validate our summarization model. This validation process explores the models capacity to improve the HCPs’ understanding of their patients’ PCC needs over time. Our dataset will also represent a range of frailty levels, comorbidity clusters, and demographic characteristics, ensuring comprehensive model training. This representativeness should suffice for early-stage model training.

Graph-based and hierarchical transfer models will be developed and compared after encounter collection. Specifically, we will produce a comparative performance metric, using ROUGE 1, for each model against a human-generated gold-standard summary. The results will indicate the strengths and weaknesses of each approach, guiding further model refinement. Human evaluators will also qualitatively assess the AI-generated summaries, providing insights on their accuracy, quality, fluency, and person-centeredness. Overall, this process will identify which model most effectively summarizes PC information from longitudinal MDT encounters and carefully reflects the unique needs of PCNs and their related community assets.

Through repeated engagement sessions, prototyping evaluations by MDT members will refine the usability and capacity of implementing the AI summarization tool. This iterative prototyping, codeveloped with local stakeholders, should enable sufficient alignment with workflow integration, IT system compatibility, regulatory compliance, and necessary training and support infrastructure for implementation. This process will also help identify necessary training needs. Stage 5 should produce an implementation strategy and training program that reflects consultation with HCPs and management teams. If a feasible prototype and implementation strategy are not achieved, a comprehensive report will be produced outlining key problems and potential solutions for implementation attempts.

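### Accuracy is promised in the Abstract and Results but absent from the Stage 4 ratings, the theme score is a bare count, and no stated step to go-live refers to Stage 4 accuracy

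*Protocol article*

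**What the plan says.** The evaluation of the AI summaries is described three times in the protocol article.

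- **Abstract, Methods:** the summaries are compared with human-written ones and "assessed for accuracy, quality, fluency, and person-centeredness". The Abstract adds that the original team members will see them for validation.
- **Methods, Stage 4:** trained, blinded evaluators rate the summaries. "They will assess their informativeness, fluency, quality, and person-centeredness (number of PC themes captured by the summaries". The automatic measure is an F1 score: "We will automatically evaluate the quality of these summaries using ROUGE".
- **Results, Stages 3 and 4:** "we will produce a comparative performance metric, using ROUGE 1, for each model against a human-generated gold-standard summary". Human evaluators also assess the summaries, "providing insights on their accuracy, quality, fluency, and person-centeredness".

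The route to live use is in Stage 5. Prototype sessions are repeated at least twice and "until saturation is reached, which is defined as broad HCP satisfaction with the usability of the devices". Next come stakeholder support, three sessions with the governance and management group (one of them on regulatory and ethical guidelines), agreement of adopters and clinical teams, training, and a final check of resources and support. The system then goes live.

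**The concern.** Stage 4 is where the graph-based and hierarchical models are compared, so its list of measures decides what counts as the better model. If accuracy is not rated there, a summary that reads well and mentions the right topics can score well while stating something the patient did not say, or the opposite of what the patient said.

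The two models may differ in exactly this respect. The graph model extracts sentences, whereas the hierarchical model builds on pretrained language models trained to predict the next word. The protocol itself recognises the hazard: Anticipated Findings names hallucinations and omission of critical facts as problems that work in this field tries to reduce, and Limitations says that human assessment is needed for accuracy.

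The step into live use matters because summaries are embedded in the electronic patient record and later summaries build on earlier ones. An early error could therefore carry forward.

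**Working it through.** No sample size, power or alpha figure is involved, and the plan gives no figure to reproduce. The check compares the sections and uses two small illustrations with invented data.

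**1. The lists of dimensions**

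| Place | Dimensions |
|---|---|
| Abstract, Methods | accuracy, quality, fluency, person-centredness |
| Results, Stages 3 and 4 | accuracy, quality, fluency, person-centredness |
| Methods, Stage 4 | informativeness, quality, fluency, person-centredness |

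One item is dropped (accuracy) and one added (informativeness). The Abstract and Results list accuracy separately from quality, so quality cannot simply be assumed to include it.

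**2. What ROUGE-1 detects**

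ROUGE-1 F1 = 2PR/(P + R), where P is matched words divided by words in the summary and R is matched words divided by words in the gold standard. The sentences are assumptions, not trial data.

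- Gold standard, 15 words: *she wants to stay at home and does not want to go back to hospital*.
- The same sentence without *not*, 14 words, all matching: P = 14/14 = 1 and R = 14/15. F1 = 2 × 1 × (14/15) / (1 + 14/15) = 28/29 = 0.966. The stated preference is reversed.
- A faithful paraphrase, 10 words, one matching: *patient prefers remaining in her own house and declines readmission*. P = 1/10 and R = 1/15. F1 = (2/150) / (25/150) = 0.08.

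The reversed sentence scores far above the faithful one. ROUGE-1 therefore cannot stand in for an accuracy rating. It is not blind to everything, because R falls when content is left out and P falls when words are added.

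**3. What the theme count detects**

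Stage 4 fixes "person-centeredness (number of PC themes captured by the summaries" as the score, with no denominator and no rule for a theme that is listed but unsupported or misstated. Suppose the gold standard has 5 themes. Model A lists 4, all correct. Model B lists 5, of which 3 are correct and 2 unsupported.

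| | A | B |
|---|---|---|
| Count, if every listed theme counts | 4 | 5 |
| Count, if only supported themes count | 4 | 3 |
| Recall (correct / gold-standard themes) | 4/5 = 80% | 3/5 = 60% |
| Precision (correct / listed themes) | 4/4 = 100% | 3/5 = 60% |

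The ranking depends on a rule that the article does not give. Even under the stricter rule, the count does not show B's two unsupported themes.

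**4. The steps to go-live**

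| Step in Stage 5 | Refers to Stage 4 accuracy? |
|---|---|
| Saturation of prototype sessions (usability satisfaction) | No |
| Stakeholder support | No |
| Session on regulatory and ethical guidelines for the strategy | No |
| Adopters, implementers and teams content with the system | No |
| Verification of resources, training and support | No |

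None of the five steps refers to Stage 4 performance or to an error limit.

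**The case against.** The other side has several good points.

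- **Accuracy is listed inconsistently; it is not absent from the plan.** Two of three descriptions include it, and the Results section says that the whole process identifies the better model. A reader might infer that the model choice will be made on measures blind to wrong or missing facts. The documents do not support that: the Results section still names accuracy, and both ROUGE F1 and a theme count respond to omissions.
- **Quality and informativeness are undefined.** A rating form may cover correctness, and an article may leave that form to a fuller document. This stands as a caution. It does not resolve the contradiction between lists that are stated here.
- **The reversal of ranking needs a particular reading.** On the natural reading a theme that the patient never raised is not captured, and A then beats B by 4 to 3. The example shows an ambiguity, not a demonstrated error.
- **Usability is not the only condition for go-live.** A reader might infer that satisfaction with the devices alone puts the system into use. It defines saturation of the prototype sessions only. The Abstract also promises validation by the original team members, testing against their standards, and integration only if the tool is judged suitable. Stage 5 allows the tool to be found unfeasible. None of these carries a stated accuracy criterion, and Stage 4 does not describe the validation step.
- **People check the output.** Stage 5 participants review and edit a summary, and in the Stage 6 Time-Motion workflow the professional checks each one before submission. That check is described as one of acceptability. It makes entry of a wrong summary into records possible, not certain.
- **The design limits invention.** The graph model is extractive and the hierarchical one uses retrieval-based selection. That lowers the risk of fabrication but leaves loss of context and wrong attribution.

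**Conclusion.** The point holds in a limited form and is a should-fix. The Stage 4 Methods contradict the Abstract and Results on whether accuracy is rated. Followed as written, Stage 4 has no measure designed to detect a false statement, and the stated progression to live use does not refer to Stage 4 accuracy. The existing human checks and the Abstract's validation step reduce the risk without closing the gap.

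The size can only be illustrated: F1 stays at about 0.97 when one word reverses the meaning, and a theme count may rank two models as 4 to 5 or 4 to 3 depending on an unstated rule. Both rest on invented examples and say nothing about how often such errors would occur. The ROUGE illustration takes the variant named in the Results section to be single-word overlap. The conclusion also assumes that no fuller rating form, not shown here, already defines quality or informativeness as factual correctness.

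**What to change.** 1. Reconcile the Abstract, Stage 4 and Results by restoring accuracy to the Stage 4 human rating. Record, per summary, the unsupported or wrong statements and the important omissions, checked against the transcript.
2. Replace the bare theme count by two proportions: correctly captured themes out of gold-standard themes (recall) and out of all themes listed (precision).
3. Report these beside ROUGE when the graph-based and hierarchical models are compared.
4. State in Stage 5 that progression to go-live also requires a Stage 4 accuracy criterion, agreed beforehand with the multidisciplinary team. The existing usability and stakeholder steps stay.

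The cost is a longer form for evaluators who are already planned, and a sentence in Stage 5. The article does not say how many summaries are rated. If every encounter's summary from both models were rated, that would be about 150 × 2 = 300 forms at three encounters per patient, so the extra minutes per form should be budgeted. The study is neither funded nor submitted for ethical review, so the text can still be changed easily.
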